##### Oscillatory analyses: Motor control data

For this study, we are especially interested in the primary motor and visual cortices bilaterally. The communication between these two distant brain areas provides the basis for integration of complex information, that helps us adapt our movement to changes in the environment [54]. Besides these two main areas, visuomotor tasks involve the supplementary motor area, the primary sensory cortex, the premotor cortex and the parietal cortex [55, 56]. Given the number of involved areas, we will include all electrodes in the oscillatory analysis. Once the data are cleaned according to the abovementioned procedures, we will divide the data according to each movement segment (reach, manipulate, withdraw). An additional segment of interest is the pre-movement segment, that corresponds to 2000 ms before the GO signal and 1000 ms after (to include the first part of motion) [57]. The EEG and behavioral data will be synchronized post-hoc using timestamps.

We will perform time–frequency analysis to investigate the power at a specific frequency band during the different segments (or epochs) of the task execution (see below). Time–frequency analysis can characterize the temporal dynamics of three of the features of oscillations contained in the EEG data: frequency, power, and phase [58]. Time–frequency power and the phase synchrony will be computed. Time–frequency power has been used to link brain activity to a variety of cognitive and motor mechanisms. Phase synchrony provides information about the timing of the oscillations at a specific frequency and can be examined across trials to capture how consistent or synchronous the phase of the oscillations is across trials [58]. Additionally, this technique provides a close interpretation of the neurophysiological mechanisms. Time–frequency analysis measures the dynamic changes in amplitude and phase of neural oscillations across different frequencies [58]. In a recent study, time–frequency analysis has been shown to be able to depict increased connectivity between the visual and motor cortex during action observation, compared to connectivity between other brain areas, whilst other techniques did not detect such pattern [59].

In this investigation, we will explore the changes in alpha, beta, and gamma frequencies. Whilst alpha power seems to predict accuracy in visuomotor tracking tasks [55], changes in beta frequency are related to movement planning and execution [60]. Increased synchronization in the high gamma-frequency range has also been shown to be related to active movement initiation [61], which may provide additional insights on the cortical dynamics of motor control.

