Motor planning and execution deficits will be evaluated during a visually guided reach-to-grasp task at different reaching depths using reflective markers attached to the fingers and hand. The participant sits in front of a wooden box (where the pegs are initially inserted) and a cylinder (where the pegs are to be inserted). The box is mounted on a tripod that can be adjusted to the participant height and arm length. There are two equally sized pegs that are placed by the experimenter in the box differing by their color on the tip of the peg. The participant is instructed to focus on the target peg (green) and ignore the flanker peg (red). The participant needs to reach and grasp the target peg by estimating its depth and insert it in the cylinder. The board on the wooden box has 2 rows of 3 holes (right on top of each other) where the pegs can be inserted. The target and flanker pegs can be inserted in the same column, with 1 or 2 column difference, to increase depth between the pegs. There will be a total of 90 trials to complete with each eye condition (dominant eye, non-dominant eye and with both eyes):(i) No depth difference: 20 trials (5 trials with target in close-top position, 5 trials with target in further-top position, 5 trials with target in close-bottom position and 5 trials with target in further-bottom position). In this condition, the flanker does not influence stereovision perception.(ii) One level of depth difference: 20 trials (10 with the target in front (5 up and 5 bottom) and 10 (5 up and 5 bottom) with the flanker in front). In this condition, the flanker may influence stereovision perception either when it is located in front or after the target peg.(iii) Two levels of depth difference: 20 trials with two levels of depth difference (10 with the target in front (5 up and 5 bottom) and 10 with the flanker in front (5 up and 5 bottom)). In this condition, the flanker may influence stereovision perception either when it is located in front or after the target peg.(iv) Only target condition: 20 trials with only the target inserted in the same locations as in the ‘no depth difference’ condition. This is the control condition to investigate the potential effect of the flanker on the position of the target.

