#### Secondary outcomes III: Brain activity

We will use a 128-channel eWave + cap connected to an amplifier (ScienceBeam, Shenzen, China) to record continuous EEG during the selective attention and motor control tasks (1000 Hz sampling rate). Electrode impedances will be kept below 50 kΩ, and electrodes will be referenced to the Cz electrode. Offline filtering will involve a 0.1 Hz high-pass, 40 Hz low-pass, as well as a 50 Hz notch using a second-order Butterworth filter (–12 dB/octave roll-off, computed linearly with forward and backward passes to eliminate phase-shift). EEG will be next screened for transient noise, eye movements, and muscle artefacts using an automatic artefact rejection criterion of ± 100 μV for adults and ± 150 μV for children, along with visual inspection. Data from artefact contaminated electrodes across all groups will be interpolated using three-dimensional splines [52].

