##### Event-related potential analyses

For event-related potential (ERP) analyses, after data cleaning, the EEG will be segmented into peri-stimulus epochs from 100 ms before stimulus onset to 500 ms after the stimulus onset. Subsequently, epochs will be averaged according to the relevant conditions, and baseline corrected. The sensory and attentional processes measured with ERPs will be analyzed with traditional analyses of ERP correlates of those mental processes (see below), followed by multivariate analysis of EEG activity elicited in the well-known time-windows of the said ERP correlates. Multivariate analyses of the EEG/ERPs focus on the reference-independent characteristics of the whole electrical field across the scalp. Here, the multivariate analyses will focus on two different measures. First, we will analyze if potential differences in EEG/ERPs across conditions and/or populations stem from modulations in the topographic EEG activity. Differences in the topography of EEG response forcibly indicate that different configurations of sources have been recruited during responses across conditions/populations of interest. The topographic analyses here will involve clustering of the group-averaged EEG/ERP activity over the time-window of the ERP components of interest. These analyses are aimed at identifying periods of stable topographic patterns (topographic maps) and differences therein across conditions of interest. After the selection of an optimal number of topographic patterns explaining the EEG data, the patterns are fit back onto single-subject data; parameters like the EEG pattern duration (or map onset, map offset) and global explained variance will be analyzed. Second, we will analyze, if the potential differences in the EEG/ERPs stem from modulations in the strength of brain responses across different conditions/populations. Global Field Power (GFP) is the standard deviation of the moment-by-moment voltage of the electrical field across the whole scalp and reflects differences in the strength of brain response, across two or more conditions, within a statistically indistinguishable brain network.

These outcomes will be measured at every time point and the assessors will not be masked to treatment allocation, as these are objective measures.

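### Raw across-trial phase consistency and VEP-window Global Field Power rise as fewer clean EEG trials remain, so unequal trial retention could be mistaken for, or hide, a neural or VR effect

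*Protocol article*

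**What the plan says.** All references are to the protocol article.

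- **Artefact rejection** (Secondary outcomes III: Brain activity): "EEG will be next screened for transient noise, eye movements, and muscle artefacts using an automatic artefact rejection criterion". The threshold is ±100 µV for adults and ±150 µV for children, with visual inspection in addition. Contaminated electrodes are interpolated.
- **GFP** (Event-related potential analyses): epochs are averaged by condition first. The measure is then defined: "Global Field Power (GFP) is the standard deviation of the moment-by-moment voltage of the electrical field across the whole scalp". Under Cortical visual responses, GFP over the VEP window is compared between eye conditions and between populations. Under the EEG subsection on selective attention, GFP is used in contrasts between distractor types.
- **Phase** (Oscillatory analyses: Motor control data): time-frequency power and phase synchrony are to be computed. Phase at a given frequency "can be examined across trials to capture how consistent or synchronous the phase of the oscillations is across trials". No particular index is named.
- **Motor-task trials** (ReGraD task description): "There will be a total of 90 trials to complete with each eye condition". Four conditions of 20 trials each follow.
- **Use** (Background, research aims): aim (f) tests VR effects on cortical responses in both cohorts, and aim (h) uses electrophysiological factors to predict treatment response. EEG outcomes are measured at every time point.

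**The concern.** Phase consistency is the length of an average vector, and GFP is a standard deviation. Neither can be negative, so random noise does not average to zero in them; it adds to them. The noise contribution shrinks as the number of accepted trials N grows. Two cells with the same underlying brain response but different N therefore have different expected values.

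N is not fixed by design, because epochs are rejected for eye movements and muscle activity. The patient cohort includes strabismus, and the attention and motor tasks are run with each eye separately. It is foreseeable, though not documented, that retention could differ by eye, visit or cohort. If patients lost more trials than controls, their phase synchrony and VEP-window GFP would look stronger with no neural difference. If retention improved from one visit to the next, a true increase could be partly hidden.

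**Working it through.** **1. Trial count in the motor task.** The stated total is 90 per eye condition. The listed conditions are "No depth difference: 20 trials", "One level of depth difference: 20 trials", "Two levels of depth difference: 20 trials with two levels of depth difference" and "Only target condition: 20 trials with only the target inserted", so 4 × 20 = 80. The stated 90 is not reproduced, and the two figures should be reconciled. The article does not say whether phase is computed within a 20-trial condition or pooled, so both are shown.

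**2. Phase consistency with no true locking.** R = |mean of exp(iθ)| over N trials, with expectation approximately √(π/(4N)):

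| N | 20 | 14 | 10 | 80 | 56 |
|---|---|---|---|---|---|
| Expected R | 0.198 | 0.237 | 0.280 | 0.099 | 0.118 |

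Simulation agrees to within about 0.002. Going from 20 to 14 trials raises R by 0.237/0.198 − 1 = 20%. Going from 80 to 56, the same 30% loss, raises it by the same proportion.

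**3. False-positive rate.** Simulated two-sample t-test, 30 v 30, one time-frequency point, no true difference, nominal 5%. The cohort size is the protocol's. The retention and locking values are assumptions.

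| Trials kept | No locking | True locking 0.2 | True locking 0.4 |
|---|---|---|---|
| 20 v 20 | 5% | 5% | 5% |
| 20 v 18 | 6% | 6% | 6% |
| 20 v 14 | about 26% | about 14% | about 7% |
| 80 v 56 | about 26% | 6% | 6% |

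A paired comparison of 30 patients at two visits with 20 v 14 trials gives about 26%, 12% and 6%. Pooling halves the absolute bias but, with no locking, leaves the error rate unchanged, because bias and sampling spread shrink together. Once there is real locking, pooling nearly removes the problem.

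**4. GFP of an averaged response.** Approximately √(S² + s²/N), where S is the true field strength and s the single-trial noise. The article gives neither, nor the number of attention-task trials, so these are illustrative assumptions, for 100 v 60 trials kept:

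- S = 3 µV, s = 10 µV: √(9 + 1.00) = 3.16 v √(9 + 1.67) = 3.27, a rise of about 3%.
- S = 1.5 µV, s = 15 µV: √(2.25 + 2.25) = 2.12 v √(2.25 + 3.75) = 2.45, a rise of about 15%.

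**5. Check of the remedy.** Pairwise phase consistency is (N·R² − 1)/(N − 1). Its simulated mean is 0.00 with no locking and about 0.04 at true locking 0.2, whatever N is. Its false-positive rate is about 5% at both 20 v 14 and 80 v 56.

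**The case against.** The strongest reply is that an article does not normally describe trial-count matching, minimum epoch numbers or the choice of a bias-corrected index. Those belong in the full protocol, the analysis plan or the trial handbook, so silence on them is no error. That stands. The phase wording describes what the technique allows and does not commit to the raw index, so the phase part of the point is conditional. The GFP part is firmer: the article does commit to GFP from averaged epochs compared across eyes and populations.

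A reader might infer that differences in data loss will appear as brain or VR effects. The documents do not support that:

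- They give no retention figures and no evidence of unequal loss.
- The adult and child thresholds do not by themselves separate cohorts that are age-matched, and would rarely change between one person's visits.
- Computing phase within 20-trial conditions is an inference. The oscillatory section divides the data by movement segment and does not mention depth condition.
- The 20-trial figure belongs to the motor task and says nothing about GFP, which comes from the attention task.
- The attention GFP contrasts (matching v non-matching colour, alone v with sound) are within person, so similar loss in both conditions largely cancels.
- Aim (g) names vision, attention and motor skills, not EEG. Aim (f) is the one that tests cortical responses directly.

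The dependence on N itself survives all of this.

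**Conclusion.** The point holds in conditional form. Raw phase consistency, if that is the index used, and VEP-window GFP both carry an upward bias that depends on the number of accepted trials. Comparisons between eyes, visits or cohorts are affected only if retention differs systematically. The effect is appreciable when true locking is weak and the gap in retention is around 30%. It fades as true locking strengthens and is negligible for a loss of about 2 in 20. The retention rates, locking strengths and voltages are assumptions, and the trial's own data may show no imbalance. The primary outcome, best corrected visual acuity, is untouched. Because the outcomes are secondary and the oscillatory part is exploratory, this is a low-priority improvement and not a flaw in the trial's main conclusion.

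**What to change.** - **Phase synchrony:** use pairwise phase consistency, or subsample at random to the same number of accepted trials in every cell compared.
- **VEP-window GFP and map-fit measures:** where these are compared across eyes, visits or cohorts, compute them from averages with matched numbers of accepted trials.
- **Reporting:** give accepted trials by eye, visit and cohort, so that a reader can see whether retention differed.
- **Trial total:** reconcile the stated 90 motor-task trials with the 80 listed.

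No new data are needed. The cost is a few lines of analysis code, a sentence in the plan and a small loss of precision where trials are subsampled.

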## Secondary outcomes IV: Adherence and safety

Adherence (total amount of training hours, regularity of training) throughout the treatment will be investigated and the visual outcome will be correlated to the adherence that is automatically recorded by the Vivid Vision Home system. By including these measures of adherence to the serious games intervention, we will obtain important information [62], as the traditional treatment is known to have low adherence [11].

At the end of the study, the frequency and type of adverse events will be analyzed and compared across groups by the researcher masked to group allocation.

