**Methods:**

The AMBER study is a randomized, cross-over, controlled trial designed to assess the effect of binocular stimulation (VR-based stereoptic serious games) in individuals with residual amblyopia (*n* = 30, 6–35 years of age), compared to refractive correction on vision, selective attention and motor control skills. Additionally, they will be compared to a control group of age-matched healthy individuals (*n* = 30) to account for the unique benefit of VR-based serious games. All participants will play serious games 30 min per day, 5 days per week, for 8 weeks. The games are delivered with the Vivid Vision Home software. The amblyopic cohort will receive both treatments in a randomized order according to the type of amblyopia, while the control group will only receive the VR-based stereoscopic serious games. The primary outcome is visual acuity in the amblyopic eye. Secondary outcomes include stereoacuity, functional vision, cortical visual responses, selective attention, and motor control. The outcomes will be measured before and after each treatment with 8-week follow-up.

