## Methods I: Participants, interventions, and outcomes

### Study design

This is a single-center, evaluator-masked, non-inferiority, cross-over Randomized Controlled Trial (RCT). This study is approved by the Ethical Cantonal Board of Geneva, Switzerland (CCER N° 2021-D0090) and all methods are performed in accordance with the relevant guidelines and regulations. The protocol for this study was designed according to the SPIRIT (Standard Protocol Elements: Recommendations for Interventional Trials) 2013 Statement [35, 36]. Recruitment of participants is planned from May 2022 to December 2024. The trial will take place in the Department of Ophthalmology of the Geneva University Hospitals (Switzerland). The amblyopic cohort will take part in the cross-over design. They will be randomly assigned to take part either first in the study-intervention arm and second in the control-treatment arm, or vice versa (AB or BA), stratified according to the type of amblyopia (anisometropic, strabismic or mixed). They are not masked to the order of the received training. The age-matched control cohort will only complete the VR-based intervention.

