At the beginning of the training, the visual contrast of objects visible to the fellow eye is decreased relative to the amblyopic eye. Each week and according to the participant’s performance, the difference in the input strength between the eyes will become smaller. The goal is to no longer need any modification of images’ features to combine them, and to perceive depth all the time. The difficulty of the games will be automatically adjusted based on an algorithm developed by Vivid Vision Inc. and integrated in the software (Smart Assist). This automatic adjustment aims at individualizing the treatment to meet the therapeutic needs of the patient. By individualizing the treatment to the patient’s needs, we hope to improve the efficacy of the treatment. To this purpose, built-in tests in the Vivid Vision Home software (Prism Tuner—to optimize the virtual prism settings for a patient’s treatment session, Stereoacuity – to estimate of the patient’s stereoscopic vision) will be performed systematically to increase or decrease the amount contrast needed for the patient to successfully play. These changes aim to keep the games challenging to the current level of visual skills of the participants. This “adaptiveness” of the games’ difficulty levels is meant to keep participants engaged and to support their improvement over the course of the whole training. Additionally, after each training session, participants or participants’ parents will report in a gaming diary, which they have been given by the experimenters, duration of their gaming session that day, their feelings about it (i.e., experiencing fun or, alternatively, difficulty during the game) as well as any adverse event (i.e., nausea, headache, diplopia). Participants will be instructed to inform the research team as soon as they experience any adverse event. Through the web-based dashboard of Vivid Vision Home, the research team will be able to see the participant’s activities, follow up on the prescribed play time and will get a notification after 2 days have passed without playing.

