## Methods III: Data collection, management, and analysis

### Data collection

All assessors will be trained to collect the study data. We have developed a handbook specific for the AMBER RCT in which all information related to the protocol is described and every study member has access to it.

The data will be collected at HUG (Geneva, Switzerland) and at the patients’ home (data collected directly from the Vivid Vision Home software and diary). General patient’s characteristics, such as age, sex and dominant eye will be recorded at baseline. Participants in the amblyopic cohort will be classified according to their type of amblyopia (anisometropic, strabismic or mixed).

All efforts will be made to promote participant retention and complete the crossover design of the study. We will phone the participants weekly while they are receiving the VR-based intervention and collect data related to their compliance and adverse events. All participants will fill in a diary in which they will report, if they have played the games of the intervention, as well as other games (and how many hours), to keep track of potential confounders. These data will be used to inform about participant retention in the study outcomes.

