### Statistical analysis

Linear Mixed Models (Jamovi & R software) will be used to investigate primary and secondary outcomes before and after treatment, compared to refractive correction, and compared to the healthy control group. We will include BCVA and stereoacuity measured at baseline and age as covariates. If age shows a significant covariance effect, we will identify clusters of age-based differences and compare the groups directly by splitting the data and using age as a factor in the analysis. For the selective attention skills, multivariate analyses will also be performed to investigate changes in brain activity (CARTOOL [65], STEN software [66], FieldTrip toolbox [67], custom scripts in Python). To evaluate motor control skills, trajectory and velocity profiles using Statistical Parametric Mapping [68] will be determined. Structural Equation Modelling will be conducted to identify the individual and combined value of behavioral and electrophysiological changes in vision, selective attention, and motor control to predict improvements in vision functions (Onyx software).

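### As worded, the adverse-event comparison is between groups that all receive VR, so it does not address the aim of comparing VR safety with standard care

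*Protocol article*

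**What the plan says.** Aim (d), in the list of research aims that closes the Background, is to assess adherence and safety of the VR intervention against standard care. Under Secondary outcomes IV: Adherence and safety, the analysis planned for the end of the study is that "the frequency and type of adverse events will be analyzed and compared across groups by the researcher masked to group allocation". No other analysis of adverse events is given.

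On who receives what:
- The Abstract (Methods) says: "The amblyopic cohort will receive both treatments in a randomized order according to the type of amblyopia".
- Study design says of the amblyopic cohort: "They will be randomly assigned to take part either first in the study-intervention arm and second in the control-treatment arm, or vice versa".
- Study design says of the healthy cohort: "The age-matched control cohort will only complete the VR-based intervention".

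On how events are collected:
- The section on the experimental intervention has participants or parents complete a diary after each training session. It covers play time, feelings about the session, "as well as any adverse event (i.e., nausea, headache, diplopia").
- Data collection says: "We will phone the participants weekly while they are receiving the VR-based intervention and collect data related to their compliance and adverse events".

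No matching diary or call for adverse events is described for the glasses period.

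**The concern.** The aim calls for a contrast of treatments: events on VR against events on glasses. The analysis sentence gives a contrast of groups, masked to group allocation. The only thing allocated in this trial is treatment order, and elsewhere the article uses *group* for the healthy cohort. Each of these sets of people is exposed to VR, so a contrast between them sets VR-exposed people against VR-exposed people.

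Similar event counts across groups are therefore what one would expect even if VR caused several times as many events as glasses. A reader of the results could take that similarity as evidence on aim (d), which it would not be. The point matters because the article itself names nausea, headache and diplopia as events to record, and it enrols children from age 6.

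**Working it through.** **1. Exposure by group (Study design; Control intervention for the control cohort)**

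| Group | VR | Glasses as the allocated treatment |
|---|---|---|
| Amblyopic, order AB | yes | yes |
| Amblyopic, order BA | yes | yes |
| Healthy cohort | yes | no |

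No row has glasses without VR.

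**2. Expected result of the order comparison**

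The article gives no adverse-event rates, so the risks below are assumptions. Let p_v be the chance that a patient has at least one event in the VR period and p_c the chance in the glasses period. Take the periods as independent, with no carry-over, period effect or dropout. Over the whole study the proportion with an event is 1 − (1 − p_v)(1 − p_c). The order of the two factors does not matter, so this is the same in AB and BA.

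| Assumed VR v glasses | AB | BA | Difference |
|---|---|---|---|
| 20% v 5% | 1 − 0.80 × 0.95 = 24% | 24% | 0 |
| 30% v 5% | 1 − 0.70 × 0.95 = 33.5% | 33.5% | 0 |
| 40% v 10% | 1 − 0.60 × 0.90 = 46% | 46% | 0 |
| 50% v 10% | 1 − 0.50 × 0.90 = 55% | 55% | 0 |

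**3. The cohort comparison**

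This sets VR plus glasses in amblyopic patients against VR alone in healthy people, who play without the between-eye contrast difference and with Smart Assist off. Any difference mixes population, game settings and the extra glasses period. It can say something about harms specific to amblyopic patients or to the dichoptic settings, but it does not estimate VR against glasses.

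**4. What the crossover can give**

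Within each amblyopic patient, classify the VR period and the glasses period as event or no event. The discordant probabilities are p_v(1 − p_c) (event on VR only) and p_c(1 − p_v) (event on glasses only). The difference between them is p_v − p_c, which is the quantity aim (d) asks about. The table gives the power of an exact McNemar test at two-sided 0.05, counting rejections that show more events on VR. The first sample is the planned 30 and the second is the 24 from the sample-size section before the dropout allowance.

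| Assumed VR v glasses | VR only | Glasses only | Power, n = 30 | Power, n = 24 |
|---|---|---|---|---|
| 20% v 5% | 0.20 × 0.95 = 0.190 | 0.05 × 0.80 = 0.040 | 25% | 15% |
| 30% v 5% | 0.30 × 0.95 = 0.285 | 0.05 × 0.70 = 0.035 | 62% | 47% |
| 40% v 10% | 0.40 × 0.90 = 0.360 | 0.10 × 0.60 = 0.060 | 68% | 55% |
| 50% v 10% | 0.50 × 0.90 = 0.450 | 0.10 × 0.50 = 0.050 | 90% | 80% |

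The trial is sized on visual acuity and states no power for adverse events, so there is no figure of the plan's own to reproduce here.

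**5. Ascertainment**

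Suppose the true risk is the same, p, in both periods, and a share s_v of events is captured on VR and s_c on glasses. The expected observed difference is then p(s_v − s_c). A diary entry after each session and a weekly call during VR, with nothing equivalent described for glasses, make s_v larger than s_c. The by-period contrast would then show more events on VR even with no true difference.

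**The case against.** The strongest reply is that *groups* is loose wording. Safety is listed among the secondary outcomes, and the Statistical analysis section says that primary and secondary outcomes will be examined against refractive correction as well as "compared to the healthy control group". The article's language on allocation is imprecise elsewhere too. On that reading the treatment contrast is already intended. This is possible and it limits the point. It does not remove it: the same Statistical analysis sentence names refractive correction separately from the healthy group, the masking to group allocation fits AB and BA best, and no text ties adverse events to a treatment period.

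A second reply is that period attribution, the estimator and the interval usually belong in the analysis plan. That is fair, and the absence of such detail from an article is not the criticism. The criticism is that the one contrast the article does state does not match its own aim.

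Two stronger readings are tempting. One is that the trial cannot detect harm from VR. The documents do not support this: the crossover provides the right contrast, events noted after a gaming session are tied to VR when reported, and the Monitoring section has each event reviewed for its relation to treatment. The other is that a VR harm would be missed at least 97% of the time. Fisher tests across groups do reject in only about 1.6% (AB v BA, 15 v 15) and 2.6% (amblyopic v healthy during VR, 30 v 30, equal VR risk) of trials at 40% v 10%. Those figures are rejection rates under no group difference, for tests the article never specifies. They are not a miss rate for the safety evaluation as a whole.

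**Conclusion.** The point holds as a mismatch between a stated aim and the stated comparison. Followed literally, comparing adverse events across groups yields an order or cohort difference. The expected AB–BA difference is zero for any VR risk, provided there is no carry-over, period effect or differential dropout. That result is algebraic and does not depend on the assumed event rates. The power figures do depend on them, and on independence between periods.

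The problem is confined to the wording of a secondary safety analysis and to how events are collected. The design, sample size and primary outcome are unaffected. It should be corrected, because the correction is cheap and the contrast as written could be mistaken for evidence on VR against standard care.

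**What to change.** Replace the comparison across groups with a comparison by treatment within the amblyopic cohort:
- Assign each event to the period in which it starts, VR or glasses, each with its 8-week follow-up.
- Report the paired risk difference with an exact 95% confidence interval, and give the interval more weight than a p value.
- Tabulate VR events in the healthy cohort separately and descriptively.

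Collect adverse events the same way in both periods, by extending the existing diary and weekly call to the glasses period. If that is not done, state that the comparison is biased towards more VR events, and restrict it to events elicited identically at the scheduled visits.

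The cost is a revised sentence or two, onset dates on the adverse-event form, and somewhat more data collection in the glasses period. Intervals will be wide at n = 30, so a lack of significance should not be reported as evidence of equal safety.
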